### Sample size calculations

We have chosen to relate the proposed sample size to the 95% CI for the adherence rate, as recommended by the Research Design Service in London. Therefore, we would need 96 participants in each arm with a 95% confidence level and a CI of 10. This translates into a total sample of 192 (ie, 96 participants in each experimental group). For this reason, we will aim to recruit at least 250 participants to account for dropouts and potential miscarriages.

### Data analysis plan

#### Descriptive statistics

We will report the number of potential participants who were eligible and refused to take part in the study. Where possible, we will report the reasons for refusing to participate.

For each experimental group, we will report the following information:Demographic characteristics (as captured by the non-validated, sociodemographic survey)Proportion of participants answering Yes to any of the Whooley questions during the baseline assessmentProportion of participants scoring at each interval of the EPDS: between 0 and 9 points, between 10 and 12 points, and 13 points or above during the baseline assessmentProportion of participants scoring 1 or more points on question 10 of the EPDS during the baseline assessment.

#### Inferential statistics

We will compare the *retrospective and momentary assessment* and the *retrospective assessment* experimental groups for differences in adherence rates, dropout rates and timeliness of data completion. For this we will use a t-test or the non-parametric equivalent.

We will compare acceptance between the two experimental manipulations by assessing differences in participants’ rankings to those questions on a 7-point Likert scale of the poststudy acceptance survey. We will also conduct a thematic analysis of the open-ended questions of this survey.

In relation to the momentary assessments, we will examine the distribution of delays between the time of notification and time of report in order to assess the effect of this delay on the ecological validity of reports.

We will analyse usage patterns through regression modelling of log data. We will analyse participants’ momentary and retrospective assessments through time-based analyses or multilevel modelling.^33 34^ We will attempt to compare if the momentary assessments had any effect on the retrospective assessments by comparing the EPDS responses given on day 1 to those given on day 6.

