##### Retrospective plus momentary assessments

In this experimental manipulation, participants will be asked to complete a combination of retrospective assessments and momentary assessments. A retrospective assessment will be defined as a single administration of the EPDS. A momentary assessment will be defined as the five momentary questions plus the two contextual questions.

Participants will be required to complete assessments for a total of 6 months, and each assessment period will consist of six consecutive days. The 6-month participation period will be calculated from the day on which the app is activated (ie, when participants enter their activation code and activate their account), and it will be divided into six intervals. All participants will receive the first notification 2 days after activating BrightSelf (ie, first assessment), while the use of the app is fresh within their minds and to give an idea of what to expect during the study. Subsequent assessment periods will be a random selection of six consecutive days within the 21–35 days following the end of the previous assessment period (in order to avoid 12 days of continuous assessments).

The assessment period will be structured as follows:Day 1: one retrospective assessment at any random time between 17:00 and 21:00Days 2–5: three momentary assessments per day, displayed at random times within each of the following intervals: 09:00–12:00, 13:00–16:00 and 17:00–20:00Day 6: one retrospective assessment at any random time between 17:00 and 21:00.

At the end of the 6-month period, participants will be sent a link via SMS or by e-mail to complete the non-validated, poststudy acceptance survey.

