#### Timeliness of data completion

We will calculate the number of assessments that were completed in response to a notification as a proportion of the total number of expected assessments. We will subdivide this outcome by using the total number of completed assessments as the denominator. We will consider that an assessment has been completed in response to a notification if it takes place within the interval corresponding to that notification (ie, before the next notification is delivered). This broad interval may raise concerns regarding the ecological validity of the report, which we will explore in our statistical analysis.

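### Looking only at the distribution of response delays cannot show whether delay affected the momentary reports, which is the stated aim

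*Protocol article*

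**What the plan says.** Under Timeliness of data completion, the protocol article counts an assessment as a response to a notification "if it takes place within the interval corresponding to that notification (ie, before the next notification is delivered"). It sees the difficulty itself: "This broad interval may raise concerns regarding the ecological validity of the report, which we will explore in our statistical analysis".

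The only analysis tied to that promise is in Inferential statistics. There "we will examine the distribution of delays between the time of notification and time of report", for momentary assessments, "in order to assess the effect of this delay on the ecological validity of reports".

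Three other statements bear on the point:

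- Under Retrospective plus momentary assessments, days 2–5 of each assessment period carry "three momentary assessments per day, displayed at random times within each of the following intervals", namely 09–12 h, 13–16 h and 17–20 h. A single EPDS prompt follows on day 6, between 17 h and 21 h.
- The same section defines the unit by its content, without a timing condition: "A momentary assessment will be defined as the five momentary questions plus the two contextual questions".
- Inferential statistics adds "We will analyse participants’ momentary and retrospective assessments through time-based analyses or multilevel modelling", and does not mention delay there.

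**The concern.** The named method and the named purpose do not fit together. The purpose is a question about an effect: does answering late change the report? The method is a summary of one variable, the delay. It never brings in the ratings or the context answers, so followed as written it leaves the question open.

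The question matters in this study. The Introduction justifies momentary data by their collection in real time and their lower exposure to recall bias. The section on retrospective versus momentary assessments rules out reminders, so no follow-up prompt shortens the delay. If women tend to answer late when busy, tired or low, late reports could differ systematically from prompt ones and blur associations with time of day, place and activity. The findings are meant to inform a larger trial, which would need to know whether late reports can be used as momentary data. As planned, the study could say how late the reports were but not whether lateness went along with different answers.

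**Working it through.** **The plan's own figure.** The article gives no figure on delay. Its only calculated figure is the sample size: "we would need 96 participants in each arm with a 95% confidence level and a CI of 10". Reading this as ±10 percentage points with an assumed proportion of 0.5, n = 1.96² × 0.5 × 0.5 / 0.10² = 96.04, which matches 96. The point here does not depend on it.

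**How late a report may be and still count.** The inputs are the clock windows for days 2–5 and the day-6 EPDS window (Retrospective plus momentary assessments) and the rule that the next notification closes the interval (Timeliness of data completion). Two assumptions are added: a notification of either type closes the window, and prompt times are uniform within their windows. The second is needed only for the means.

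Shortest window = earliest next prompt − latest current prompt. Longest window = latest next prompt − earliest current prompt. Mean window = difference of the two midpoints.

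| Prompt | Number per period | Shortest | Longest | Mean |
|---|---|---|---|---|
| Morning to afternoon, days 2–5 | 4 | 13 − 12 = 1 h | 16 − 9 = 7 h | 14.5 − 10.5 = 4 h |
| Afternoon to evening, days 2–5 | 4 | 17 − 16 = 1 h | 20 − 13 = 7 h | 18.5 − 14.5 = 4 h |
| Evening to next morning, days 2–4 | 3 | 33 − 20 = 13 h | 36 − 17 = 19 h | 34.5 − 18.5 = 16 h |
| Evening of day 5 to day-6 EPDS | 1 | 41 − 20 = 21 h | 45 − 17 = 28 h | 43 − 18.5 = 24.5 h |

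Mean over the 12 prompts: (8 × 4 + 3 × 16 + 24.5) / 12 = 104.5 / 12 = 8.7 h. Four of 12 windows (33%) exceed 12 h. A simulation of 200,000 assessment periods gave the same limits and means.

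**Whether the delay distribution can answer the question.** Two artificial settings were given the same delays: exponential with mean 3 h, capped at the window. In one, delay has no influence on the report. In the other, the weight of the true state at prompt time falls as exp(−0.3 × delay in hours).

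| | No effect of delay | Effect of delay |
|---|---|---|
| Median delay (IQR) | 2.0 h (0.87–3.45) | 2.0 h (0.87–3.45) |
| Correlation of report with true state, delay under 0.5 h | 0.89 | 0.84 |
| Correlation of report with true state, delay over 4 h | 0.89 | 0.17 |

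The delay distribution is identical by construction, and that is the lesson: the same distribution fits an effect and no effect. The mean delay and rate of decay are assumptions, not document figures. The correlations show only the logic, because the trial never observes the true state.

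**The case against.** **The distribution is not irrelevant.** If real-time collection is what makes momentary data valuable, the share of reports answered promptly bears directly on their ecological validity. This stands. The distribution should be kept, and it shows how large the problem could be. It still does not show an effect.

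**A condensed article need not list covariates, cut-offs or sensitivity sets.** This also stands. Delay could enter the multilevel models in a fuller document, and silence on that is no finding. What remains is a stated method paired with a purpose it cannot serve.

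**Stronger readings that the documents do not support.** A reader might infer that late reports enter the momentary models unmarked and are treated as real-time data. The article does not say so. The next-notification rule is written for the timeliness outcome, the planned delay analysis implies that the delay of each report is known, and prompted and spontaneous reports can be told apart. A reader might also take the mean window of 8.7 h as expected lateness, but it is only what the rule permits; the article has no data on delays. Nor does the text say that only a notification of the same type closes a window, which would leave the last day-5 window open far longer.

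**Modelling delay would not prove validity either.** Correct. A slope of mean rating on delay would be zero if late reports were merely noisier, and non-zero if women who feel low answer late but accurately. This limits what the remedy may claim and is why variability should be examined as well as level.

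**Conclusion.** The concern holds in a limited form. Examining the distribution of delays alone does not meet the stated aim of assessing the effect of delay on ecological validity. The rule for counting responses permits delays of up to 7 h for the eight daytime prompts, 19 h for three evening prompts and 28 h for the last day-5 prompt in each period. These limits assume that a notification of either type closes the window; the 8.7 h mean also assumes uniform prompt times. How late reports will actually be, and whether late ones are excluded from the momentary models, cannot be told from the article.

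The weight is minor to moderate. This is a feasibility study, the momentary questions are declared unvalidated with no validation attempted, and adherence, dropout and sample size do not depend on this analysis.

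**What to change.** 1. Keep the distribution of delays as description.
2. Add delay to the planned multilevel models of the five momentary items, split into each woman's mean delay and her deviation from it, with prompt slot and study day. Report the within-woman coefficient with its 95% CI, and examine whether within-person variability, as well as level, changes with delay.
3. Repeat the momentary analyses on reports answered within a short prespecified delay (for example 30 and 60 minutes), and state whether later reports belong to the main momentary analysis.
4. State whether the context answers refer to the time of the prompt or the time of the answer. The wording under Non-validated, contextual questions can be read as prompt time, so this should be settled before reports are indexed by either time.
5. Report the results as associations: delay is not randomised and the true momentary state is not observed.

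If this work is not wanted, reword the aim to say that delays will be described.

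The cost is a change of wording and a little more analysis. The planned delay analysis already needs both notification and report times, so no new data are required.

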##### Retrospective versus momentary assessments

Participants will be asked to complete monthly assessments at irregular intervals for 6 months. Whenever an assessment is due (as per the sampling protocol), a notification will be displayed on a participant’s handset. There will be two types of notifications: one for the *Check Back* feature and one for the *Check In* feature of BrightSelf. The visual appearance of the notifications will depend on the operating system and on the model of the participant’s handset. The text of the notifications, however, will remain constant across participants for each type of notification.

Participants will be able to respond (and thus complete the corresponding assessments) or to dismiss the notifications. In addition, participants will be able to leave notifications unanswered. If participants do not complete an assessment in response to a notification, they will not receive reminders or follow-up notifications. In these instances, the non-response will be recorded in our database and will be coded as such for the purposes of our data analysis.

Outside assessment periods, participants will be able to use BrightSelf in any way they find convenient and there will be no restrictions on the number of assessments they can complete on a single day. However, we will be able to distinguish between assessments completed in response to a notification and those completed spontaneously. At baseline, participants will be randomly allocated to one of two types of assessment strategies:

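### Comparing Day 1 with Day 6 EPDS in the combined arm can understate an effect of momentary assessment that lasts into the next period

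*Protocol article*

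**What the plan says.** The Abstract (Methods and analysis) lists, among the study's questions, whether momentary assessments affect retrospective data. The Inferential statistics section gives one contrast for it, "by comparing the EPDS responses given on day 1 to those given on day 6". The sentence before it says that momentary and retrospective assessments will be analysed by time-based methods or multilevel models, but does not link these to this question. The comparisons between arms in that section cover adherence, dropout, timeliness and acceptance. EPDS scores are not among them.

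The schedule is under Retrospective plus momentary assessments. Of the participation period it says that "it will be divided into six intervals", and that "each assessment period will consist of six consecutive days". Days 1 and 6 each carry one EPDS. Days 2 to 5 carry "three momentary assessments per day, displayed at random times within each of the following intervals". The first prompt comes two days after activation. After that, "Subsequent assessment periods will be a random selection of six consecutive days within the 21–35 days following the end of the previous assessment period"; the only reason given for the gap is to stop two periods running into each other.

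Under Retrospective versus momentary assessments, the app may be used freely outside these periods and "there will be no restrictions on the number of assessments they can complete on a single day". The Randomisation section says that Check In is switched off in the retrospective arm, which still has one EPDS per period. Under Sample selection and recruitment, every woman completes a baseline EPDS on a tablet before the app is installed.

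**The concern.** A before-and-after comparison shows the effect of what lies between only if the first score is free of that effect. Here that is assured, as far as scheduled prompts go, only in the first period. In later periods the Day 1 score comes from a woman who has already been through one or more rounds of momentary sampling. If repeated sampling changes how she answers the EPDS, for example by making her more aware of her mood, and part of that change is still there weeks later, it is in both scores of the pair.

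The question has practical weight. EPDS bands trigger the alerts in the Duty of care section, and the Conclusion says that the findings will inform a larger trial. A small Day 6 minus Day 1 difference could be taken as evidence that Check Ins can be added without altering EPDS scores, when the contrast is weak against a lasting change.

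**Working it through.** The plan gives no figure for this contrast. Its one calculated number, 96 per arm, reproduces as 1.96² × 0.5 × 0.5 / 0.10² = 96.04, taking a proportion of 0.5 and reading the interval as ±10 points. It concerns adherence and plays no part below.

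**Exposure before each Day 1.** Four days × three prompts = 12 scheduled Check Ins per period. Before Day 1 of period k there have been 12(k − 1):

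| Period | 1 | 2 | 3 | 4 | 5 | 6 |
|---|---|---|---|---|---|---|
| Scheduled Check Ins before Day 1 | 0 | 12 | 24 | 36 | 48 | 60 |

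Five of the six Day 1 scores follow scheduled exposure. Voluntary Check Ins can only add to this, and may precede the first Day 1 as well.

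**What the contrast recovers.** Three assumptions, none of them in the documents:
- the effect on the EPDS is d and is complete by the first Day 6;
- a share r of it is still present at each later Day 1, and it is back to d by each later Day 6;
- the six Day 6 minus Day 1 differences are averaged with equal weight.

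The first pair then shows d and each of the other five shows d − rd = (1 − r)d. The mean is d × (1 + 5(1 − r))/6. A comparison of combined-arm Day 1 with the unexposed arm from period 2 shows rd.

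| r | Mean of six pairs, share of d | Each pair in periods 2–6 | Between-arm Day 1, periods 2–6 |
|---|---|---|---|
| 0 | 6/6 = 100% | 100% | 0% |
| 0.25 | 4.75/6 = 79% | 75% | 25% |
| 0.5 | 3.5/6 = 58% | 50% | 50% |
| 0.75 | 2.25/6 = 38% | 25% | 75% |
| 1 | 1/6 = 17% | 0% | 100% |

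The last two columns sum to d in every row, so the two contrasts complement each other.

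**A different shape of effect.** If each period adds the same amount d and nothing fades, Day 6 exceeds Day 1 by d in all six pairs and the mean is d. That increment is not lost.

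**Number of pairs.** The first Day 6 falls on day 2 + 5 = 7 after activation. Each later period adds its gap plus 5 days. If all six days must lie within days 21–35, the gap to Day 1 is 21–30 days and the sixth Day 6 falls between 7 + 5 × 26 = 137 and 7 + 5 × 35 = 182. If a period may start on any of days 21–35, the latest is 7 + 5 × 40 = 207, so some women may have fewer than six pairs within 6 months. With five pairs and r = 1 the recovered share would be 1/5 = 20%, which changes little.

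**The case against.** The strongest reply is that the article does not say how the pairs from different periods will be combined. It names Day 1 and Day 6, and the preceding sentence mentions multilevel modelling, which leaves room for period terms. The equal-weight average above is an assumption, and a condensed article may leave such detail to the full plan. This stands, and the percentages are therefore conditional. It does not remove the point: the contrast chosen for this question is within one arm, with Day 1 as reference and no restriction by period, and a model with only a common day effect would face the same carry-over.

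A reader might go further and infer that the plan treats Day 1 as unexposed in all six periods, that a lasting effect cancels in five of six pairs, or that the contrast can see only transient effects. The documents support none of these. The text makes no statement about exposure on Day 1. Full cancellation in five pairs needs an effect that is complete in the first period and persists entirely. Even then the first pair keeps it, leaving 17% in the average, and at r = 0.5 more than half remains.

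Two further replies also stand. The analysis is announced as an attempt, in a feasibility study sized on adherence, and no section plans to conclude that the EPDS is unaffected. And the first pair is not a clean substitute: Check In is available from activation, and if activation happens at the recruitment visit, the tablet EPDS and the first Day 1 and Day 6 scores fall within about a week, with overlapping 7-day recall.

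**Conclusion.** The point holds in a limited form. Day 1 against Day 6 is a legitimate short-term, within-period contrast, but as the only contrast named for the effect of momentary on retrospective assessment it is weak against an effect that lasts from one period to the next. Under the averaging and early-effect assumptions it recovers between 100% (r = 0) and 17% (r = 1) of the effect, with 58% at r = 0.5. Nothing in the documents says where r lies, and an effect that adds equally each period is not attenuated. That five of six Day 1 scores follow at least 12 scheduled Check Ins comes directly from the schedule, if all six periods take place. The randomised arm without Check In could reveal a lasting effect, and the section does not use it for EPDS scores. The matter is confined to an exploratory analysis; adherence and sample size are unaffected.

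**What to change.** Two changes to the Inferential statistics section:

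1. Describe Day 1 versus Day 6 as a short-term contrast within a period. Fit all pairs in one multilevel model with day, period and day-by-period terms. Show period 1 separately, but not as the main contrast.
2. Add a comparison of EPDS between the randomised arms, combined-arm Day 1 against the retrospective-arm score, by period from period 2 onwards, adjusted for the baseline tablet EPDS. This is the contrast that can detect a lasting effect.

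No new data are needed; the cost is in wording and interpretation. Three limits should be stated:
- The first pair rests on one difference per woman, so it is less precise than a pooled estimate, and it may follow voluntary Check Ins.
- The combined arm completes two EPDS per period and the other arm one. The between-arm contrast therefore estimates the effect of the whole combined protocol, not of the Check Ins alone.
- Same-numbered periods may not coincide in time. For equal gaps, Day 1 of period k falls 5(k − 1) days later in the combined arm, which is 5 days in period 2 and 25 in period 6. A term for time since activation would allow for this.

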### Timeline

We expect participant recruitment to start in January 2017, and the last follow-up to take place in August/September 2017 (assuming a recruitment period of 2 months and a half).

